## Abstract

**Background:**

Actively referring smokers to smoking cessation (SC) services could increase quitting and is scalable for the population. The objective of this study is to compare 2 different intensities of SC active referral for smokers in the community of Hong Kong.

**Methods/design:**

This is a single-blind, parallel 3-armed cluster randomized controlled trial (cRCT) consisting of high-intensity SC active referral (HAR Group), low-intensity SC referral by text messaging on promoting SC services use (Text Group) and a control group receives general very brief advice. Biochemically validated daily smokers will be proactively recruited in the community from 68 clusters (recruitment sessions). The primary outcome is self-reported 7-days point prevalence abstinence (PPA) at the 3- and 6- month follow-ups. Secondary outcomes are SC service use, smoking reduction rate (SRR, daily cigarette consumption reduced by ≥50%; excluding quitters) and biochemically validated quit rate (exhaled CO < 4 ppm and salivary cotinine < 10 ng/ml). Outcome assessors and data analysts will be blinded to group allocation. Intention-to-treat principle and Generalized Estimating Equation (GEE) regressions will be used for data analysis.

**Discussion:**

This will be the first trial on evaluating the efficacy of the 2 different intensities of SC active referral on smoking cessation in community smokers. It is anticipated that the results from this trial can provide evidence to the effectiveness of high-intensity active referral to SC services and low intensity SC referral by using text messaging in achieving smoking abstinence.

**Trial registration:**

ClinicalTrials.gov Identifier: NCT02804880, June 17, 2016.

## Background

Despite decades of public health education and interventions on smoking cessation (SC), tobacco use remains the leading cause of preventable death causing over 7 million deaths worldwide every year [1]. Recent data indicates a decrease in the overall smoking prevalence but still with around 615,000 daily cigarette smokers in Hong Kong in 2017 [2]. Evidence has shown that smokers received SC services increases successful rate in quitting [3–6]. Although a variety of free SC services (e.g. quit-lines, clinics) are available in Hong Kong, the utility rate is low and only 14.2% of smokers had ever used [2]. Low-cost, easy accessibility and effective SC services are warranted to provide advice, medication, and support for people to quit smoking [7].

Referring smokers to SC services is one of the cheap and scalable strategies that can maximize usage of public cessation counselling and treatment. Most of current SC services depend on passive referral strategies that require smokers to seek assistance on their own, such as calling the quit-line or attending the SC clinics [8]. Unlike passive referrals that rely on smokers’ self-initiation, active referral emphasizes physicians or other healthcare professionals efforts to refer smokers to SC services directly [9, 10]. Allowance for smokers to choose their preferred service providers and cessation methods might also improve smokers’ engagement in the service and hence enhance the outcomes [11]. Proactive referral approach can help overcome the barrier of self-initiation as most community smokers quit on their own without SC services [12]. Our previous randomized controlled trial (RCT) showed that moderate active referral of SC services significantly increased smoking abstinence rate at 6 months when compared with brief general SC advice (17.2% vs. 11.5%, *p* = 0.02) [11].

Comparing with traditional telephone cessation assistance, interventions delivered via text messaging are more convenient and accessible, which could potentially extend the reach to SC services [4] and promote SC [13–15]. A recent meta-analysis of 15,593 smokers (20 RCTs) showed that the overall odds of smoking abstinence in text messaging group were 1.37 times higher than the control group [16]. The intensity of interventions in previous RCTs varies, in terms of the frequency, intensity and duration of text messaging in the intervention period, the degree and methods for personalization and tailoring of the text messaging. Substantial evidence has shown that intensive interventions produce more abstinence than less intensive interventions in the clinical setting [4]. Therefore, it is assumed that active referral intervention delivered via high-intensity text messaging will also result in more abstinence when compared with low-intensity text messaging. This study aims to evaluate the effectiveness of 2 different intensities of active referral interventions: (1) high-intensity active referral to SC services and (2) low-intensity SC service referral by using text messaging. The control group will receive general brief SC advice.

## Methods/design

### Overview of design

This is a single-blinded, parallel 3-armed cluster RCT (cRCT) on 1200 smokers participated in the Hong Kong 7th “Quit to Win” (QTW) Contest conducted in 2016–17. The QTW Contest [11, 17–20] is organized by the Hong Kong Council on Smoking and Health (COSH) each year since 2009 to promote SC in the general community. Based on the recruitment sessions, participants will be randomly assigned to 1 of the following 3 conditions: (1) high intensity active referral to SC services (HAR Group); (2) low intensity SC service referral using text messaging on promoting and encouraging SC service use (Text Group); or (3) general brief SC advice (Control Group). All participants will receive a 12-page self-help SC booklet at baseline. HAR Group and Text Group will also receive AWARD model guided SC advice with a warning leaflet and a referral card. Control Group will only receive general brief advice at baseline. The trial will follow the Consolidated Standards of Reporting Trials (CONSORT) criteria for the design [21] and is shown in Fig. 1.

**Fig. 1 Fig1:**
[figure not shown]
Study design

### Participants

Inclusion criteria:Hong Kong residents aged 18 or above;Currently smoking at least 1 cigarette per day in the past 3 months;Able to communicate in Cantonese (and read Chinese);Exhaled carbon monoxide (CO) 4 ppm or above as validated by CO Smokerlyzer;Intend to quit or reduce smoking [22];Having a local phone number for follow-up.

Exclusion criteria:Having physical or cognitive difficulties in communication;Currently following other SC programs.

### Recruitment

A total of 68 recruitment activities will be organized in all 18 Hong Kong districts aiming to recruit 1200 participants over 3 months. University students majoring in nursing, public health and related fields and volunteers of non-governmental organizations (NGOs) will be trained as SC ambassadors in a two-day workshop (8 h each) for onsite recruitment. To reach as many as eligible smokers, booths containing SC and recruitment information will be set up in shopping malls and public areas. Using persuasive techniques such as the ‘foot-in-the-door’ method [23], SC ambassadors will ask smokers simple questions (e.g., daily cigarette consumption, history of smoking, general health status) to arouse their interest in participating in the Contest. Informed consent for voluntary participation will be obtained from the eligible participants before administering the baseline questionnaire.

### Randomization and blinding

cRCT design will be used in which all participants will be randomly assigned to 1 of the 3 groups based on the recruitment session. The randomization of group assignment will be generated before recruitment. One investigator who does not participate in recruitment will randomly generate blocks, with each block size equal to 3, 6 or 9, containing a random permutation of the 3 RCT groups. The numbers for the permutation in the blocks will be generated from the website http://www.random.org (a website for generating random integers), and then merge with the list of all recruitment days. As the intervention cannot be completely blinded in this study, the RCT is single-blinded that all outcome assessors and data analysts will be blinded to group allocation.

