#### On-site active referral for HAR group

Interventions in HAR group are designed to promote the use of the existing SC services to increase abstinence. Five major cessation services in Hong Kong will be involved. They had successful collaboration with the Contest in 2015, and their characteristics were reported previously [11, 25]. Well-trained SC ambassadors will assist on-site booking for SC services based on participants’ preferred services providers and available time. For participants who are not ready to seek SC services at on-site, they will be encouraged to set a date for appointment booking. SC ambassadors will follow them through the telephone at 1 week. They can also inform us through instant messages or telephone calls anytime between 1-week and 1-month. SC ambassadors will help participants book the appointment once receiving their decisions on SC services providers, preferred time and clinics.

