### Data collection

#### Baseline

The baseline questionnaire data includes four parts and will be collected by trained SC ambassadors. The first part measures participants’ smoking status (e.g., average number of cigarettes smoked per day, the age of starting smoking and the usual time having the first cigarette smoked each day, attempts to quit or reduce, methods used in past quitting attempts, etc.). The second part measures participants’ readiness to quit, and perceived importance, difficulties and confidence to quit smoking. The third part asks participants’ knowledge about smoking (e.g., e-cigarette and risk of smoking). The final part collects sociodemographic data (e.g., sex, age, education level, number of children, occupation, marital status, annual income, etc.).

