### Data analysis

Data will be entered into SPSS for Windows (version 23). Descriptive statistics such as frequency, percentage, and mean will be used to summarise the outcomes and other variables. The main analysis will be a comparison between both intervention groups and the control group for the proportions of smoking abstinence at 3 and 6 months, using chi-square tests and odds ratios with 95% confidence intervals. Generalized Estimating Equation (GEE) models will be applied to test the intervention effect, to identify the baseline predictors of successful quitting and to assess the changes in smoking-related factors over time. Intention-to-treat (ITT) analysis will be used in which participants who lose contact or drop out in the follow-ups will be treated as a failure to achieve any cessation outcome. Multiple imputations will be used to compute missing data for outcome variables.

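### Session arms are fixed before smokers are approached and no concealment from recruiters is described, yet the comparison labelled main is a crude chi-square test that uses neither sessions nor baseline predictors

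*Protocol article*

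**What the plan says.** **Allocation.** Under Randomization and blinding, "all participants will be randomly assigned to 1 of the 3 groups based on the recruitment session". On timing, "The randomization of group assignment will be generated before recruitment". The permuted numbers are drawn by an investigator outside recruitment, "and then merge with the list of all recruitment days". The same section limits blinding to outcome assessors and data analysts.

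**Recruitment.** Under Recruitment, trained ambassadors staff booths in malls and public areas and use persuasive techniques; "SC ambassadors will ask smokers simple questions" to raise interest. Consent comes before the baseline questionnaire, but the person who takes it is not named. One inclusion criterion under Participants is "Intend to quit or reduce smoking".

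**Delivery.** In the section on on-site active referral, "Well-trained SC ambassadors will assist on-site booking for SC services". The sections on AWARD advice and on general brief advice do not say who delivers them.

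**Baseline data.** Ambassadors collect smoking history, including cigarettes per day, time of first cigarette and past quit attempts, as well as "readiness to quit, and perceived importance, difficulties and confidence to quit smoking".

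**Analysis.** Data analysis gives the main comparison of each intervention group with control as one made "using chi-square tests and odds ratios with 95% confidence intervals". A separate sentence applies GEE to test the intervention effect, to find baseline predictors of quitting and to follow changes over time. It names neither a clustering unit nor adjustment covariates.

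**The concern.** Randomising sessions balances sessions in expectation. It does not balance the individuals enrolled afterwards by staff who may know the session's arm. Here recruitment is discretionary, and one eligibility criterion concerns motivation, which is open to judgement and plausibly related to quitting.

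If ambassadors at HAR sessions ended up persuading readier smokers than those at control sessions, part of the abstinence difference at 3 and 6 months would reflect who was recruited. The shift could also run the other way and hide a real effect. Intention-to-treat analysis keeps everyone in the arm in which they were enrolled, so it cannot undo selection that came before enrolment. A crude chi-square test offers no protection against it, although the trial collects variables that could absorb part of the imbalance. The test also treats participants as independent when sessions were randomised.

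**Working it through.** **1. The article's own figure.** Inputs from Sample size and power analysis: 3-month abstinence 14% and 18.7%, 5% significance, 80% power. For two proportions, with a two-sided test, pooled variance under the null and no continuity correction:

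n = [1.96·√(2·p̄·(1−p̄)) + 0.8416·√(p₀(1−p₀) + p₁(1−p₁))]² / (p₁−p₀)²

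With p̄ = 0.1635 and p₁−p₀ = 0.047, n = 970.7, rounded up to 971 per arm. The stated figure is reproduced exactly, and it is an individual-level calculation. The point made here disputes no stated figure; this step fixes the test and the control rate for what follows.

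**2. What a difference in case mix would do.** The documents give no share of motivated smokers and no quit rates by motivation, so these are assumptions:
- no true intervention effect, and control abstinence 14%;
- half of control recruits are motivated;
- motivated smokers quit at r times the rate of the others, with r = 1.5, 2 or 3;
- the motivated share is higher by s = 5, 10 or 20 points in the intervention arm.

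The quit rate of the less motivated is L = 0.14 / (0.5r + 0.5), and that of the motivated is rL. The intervention arm's expected rate is q = (0.5 + s)·rL + (0.5 − s)·L. The rejection rate is that of the two-sided 5% test at 400 per arm (both tails, normal approximation, clustering ignored).

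| r | s | q | Crude odds ratio | Rejection rate |
|---|---|---|---|---|
| 1.5 | 5 points | 14.3% | 1.02 | 5.1% |
| 1.5 | 10 points | 14.6% | 1.05 | 5.6% |
| 1.5 | 20 points | 15.1% | 1.09 | 7.3% |
| 2 | 5 points | 14.5% | 1.04 | 5.4% |
| 2 | 10 points | 14.9% | 1.08 | 6.6% |
| 2 | 20 points | 15.9% | 1.16 | 11.5% |
| 3 | 5 points | 14.7% | 1.06 | 5.9% |
| 3 | 10 points | 15.4% | 1.12 | 8.6% |
| 3 | 20 points | 16.8% | 1.24 | 19.5% |

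Worked example for the last row: L = 0.14/2 = 0.07 and rL = 0.21, so q = 0.7 × 0.21 + 0.3 × 0.07 = 0.168. The standard error of the difference is 0.0255. Upper tail: Φ((0.028 − 1.96 × 0.0255)/0.0255) ≈ 0.194. The lower tail adds about 0.001, giving 0.195.

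The spurious differences run from 0.3 to 2.8 points, against the 4.7 points (18.7 − 14) behind the 971.

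**3. Clustering, a separate matter.** There are 1200/68 = 17.6 participants per session on average. The documents give no intracluster correlation. At an assumed 0.01 the design effect is 1 + (17.65 − 1) × 0.01 = 1.17, and a nominal 5% test that ignores sessions has a true error rate of about 7.0%. At 0.05 the figures are 1.83 and 14.8%. These are not included in the table.

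**The case against.** **Roles.** A reader might infer that the same ambassadors choose, screen and consent smokers and deliver every arm, knowing the arm throughout. The article does not say so. It names ambassadors for recruitment, baseline data and HAR booking. It does not name who takes consent, who judges intention to quit, or who gives the AWARD or control advice. Knowledge of the arm before consent is an inference from silence. What stands is that recruiters are not among those blinded and no concealment at enrolment is described. The independent sequence generator and the varying block sizes (3, 6 or 9) protect the sequence, not enrolment into a session already allocated.

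**Uniform procedure.** One recruitment procedure, one carbon monoxide threshold and one intention criterion apply in all arms. The longer on-site work in HAR could make approach more selective or less so. That is fair: neither the occurrence nor the direction of bias can be shown.

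**Operational detail.** When an arm is released, in what order steps are scripted and whether a screening log is kept are matters an article commonly leaves to the full protocol. This stands, so their absence is not counted as a defect.

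**GEE is planned.** It is, in both the abstract and Data analysis, and a covariate list commonly belongs in the SAP. Nor is an unadjusted primary analysis an error in itself. But the article does fix which comparison is main, and in a trial randomised by session that is the crude one.

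**Conclusion.** The point holds as a route by which bias could enter, combined with a main analysis poorly matched to the design. Session arms precede the identification of participants, no concealment from recruiters is described, and the comparison named as main uses neither the randomised unit nor the prognostic data collected.

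It would go too far to say that selective recruitment will pass into the primary result: nothing shows that it occurs. Its size cannot be computed from the documents. Under the stated assumptions the false-positive rate lies between 5.1% and 19.5%. A 5-point difference in motivated share is nearly harmless (5.1% to 5.9%), and only a 20-point difference combined with a threefold quit-rate ratio reaches the top of the range. These figures depend on the assumed half-motivated control group, the quit-rate ratios and the neglect of clustering. The case for changing the main analysis does not depend on them, because it would respect the unit of randomisation in any event.

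**What to change.** **Data analysis.** Make the main estimate a GEE with recruitment session as the clustering unit, adjusted for a named set of baseline variables already collected: cigarettes per day, time to first cigarette, past quit attempts, readiness and confidence. Report the chi-square test and crude odds ratio as supportive. State that the adjusted odds ratio is conditional on these covariates, so that it is not read as interchangeable with the crude one.

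**Recruitment and Randomization and blinding (secondary).** State that the eligibility check, consent and baseline questionnaire are completed under one arm-neutral script before any arm-specific content. This also protects the adjustment, since ambassadors themselves record readiness and confidence.

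**Cost.** Wording only, with no extra participants, staff or data items. Adjustment removes only measured imbalance, and staff know the arm after the first enrolment in a session, so the risk is reduced and not eliminated.

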### Sample size and power analysis

The computer program G*Power is used to calculate the sample size [24]. The proposed sample size is based on the primary outcome of self-reported 7-day point prevalence of abstinence (PPA) at 3 months. Based on the QTW study in 2015, the 3-month PPA for the moderate-intensity active referral intervention and the control group was 18.7 and 14%, respectively [11]. Therefore, the effect size (odds ratio) for the intervention in the present study is set conservatively at 1.33. To detect a significant difference in quit rate with a power of 80% and a significance level of 5%, 971 participants in each arm are required. Given the limited resources and recruitment period, the maximum total sample size is 1200 (400 per group). The *p*-value and the power for testing the expected effect size (1.54) will be 0.08 and 57.3%.

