#### Text messaging for Text group

The text-messaging intervention aims to motivate smokers to book the SC appointments by themselves. They will be introduced (using the referral card) and motivated to use the SC services at onsite. IM/SMS messages (3 per week in the first month, then 1 per week in the second month) will be sent to encourage them to book an SC appointment since initial contact. A total of 16 messages will be sent to the smokers. The messages will be simpler and more generic than the messages in HAR group. Research staff will monitor the SC services use at each follow-up (1-, 2-, 3- and 6-months) and encourage smokers to book or re-book the appointment if necessary. This is a much cheaper and brief method than HAR group.

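### The sample-size section gives one required size and one power for two interventions of different intensity; neither is shown to apply to Text versus Control, and the effect is not shown to be conservative for Text.

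*Protocol article*

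**What the plan says.** The section on sample size and power in the protocol article starts from one earlier result: "the 3-month PPA for the moderate-intensity active referral intervention and the control group was 18.7 and 14%, respectively". From this it concludes that "the effect size (odds ratio) for the intervention in the present study is set conservatively at 1.33", and for 80% power at the 5% level it states that "971 participants in each arm are required". It then says that resources limit the trial to 1200 participants, 400 per group, and gives a p-value of 0.08 and a power of 57.3% for an expected effect size of 1.54. The 1.54 has no stated source and is not assigned to an arm.

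There are two interventions. The Data analysis section says: "The main analysis will be a comparison between both intervention groups and the control group". HAR is the high-intensity arm, with on-site booking, telephone follow-up and daily tailored messages for a month. Text is labelled low intensity: participants book for themselves, prompted by 16 messages over two months. Of these the article says: "The messages will be simpler and more generic than the messages in HAR group". No effect, size or power is given for Text v Control.

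Two statements in the Background bear on this. One is that "intensive interventions produce more abstinence than less intensive interventions in the clinical setting". The other is a meta-analysis of 20 trials in which "the overall odds of smoking abstinence in text messaging group were 1.37 times higher than the control group".

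**The concern.** The planning effect belongs to a third intervention, of moderate intensity, which is in neither arm of this trial. The Discussion describes it as collecting smokers' details and passing them to providers for follow-up. The protocol's ordering places HAR above it and Text below it. An effect borrowed from the middle of that ordering may be cautious for the upper arm. It cannot be called conservative for the lower arm without further argument, and none is given. The section nevertheless applies one size to every arm and quotes one power without limiting it to a comparison.

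The stake is interpretation. A reader who takes 57.3% as the power of each main comparison will give too much weight to a non-significant Text v Control result. Beside a significant HAR result, it could be read as showing that the cheaper, low-intensity referral does not work.

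**Working it through.** **Inputs.** From the sample-size section: 18.7% and 14%; 80% power; 5% level (two-sided reproduces the stated size; the article does not state sidedness); 971 per arm; 400 per group; effect sizes 1.33 and 1.54; power 57.3%. From the Background: odds ratio 1.37 for text messaging. Odds ratios of 1.25 and 1.20 are my assumptions, used to show a range. All results treat participants as independent, with no allowance for the 68 recruitment sessions as clusters.

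**Formulas.** Let d = p1 − p0, p̄ = (p1 + p0)/2, A = √[2p̄(1 − p̄)] and B = √[p1(1 − p1) + p0(1 − p0)].

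- Size per arm: n = (1.96·A + 0.8416·B)² / d²
- Power: Φ[(d·√n − 1.96·A) / B]
- Rate implied by an odds ratio: p1 = OR·o / (1 + OR·o), with o = 0.14/0.86 = 0.1628

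**Step 1: reproduce 971.** With p1 = 0.187 and p0 = 0.14: d = 0.047, p̄ = 0.1635, A = 0.5230, B = 0.5219. Then n = (1.0251 + 0.4393)² / 0.047² = 970.7, so 971, an exact match. A true odds ratio of 1.33 on 14% gives 17.8% and needs 1,455. So the 971 is the 2015 moderate-intensity effect with no reduction. Its odds ratio is (0.187/0.813)/(0.14/0.86) = 1.41. The 1.33 corresponds to its risk ratio, 0.187/0.14 = 1.336.

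**Step 2: check the stated power.** Odds ratio 1.54 on 14% gives p1 = 0.2004, d = 0.0604, A = 0.5315, B = 0.5298. At n = 400, Φ[(1.2089 − 1.0417)/0.5298] = Φ(0.316) = 62.4%. The stated 57.3% does not reproduce. The 2015 rates give Φ[(0.940 − 1.0251)/0.5219] = Φ(−0.163) = 43.5%. If those rates were observed at 400 per group, the two-sided p-value would be 0.072; with odds ratio 1.54 it would be 0.023.

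**Step 3: range for Text v Control.** The article gives no planning effect for this comparison, so each row is an assumption.

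| Assumed odds ratio | Abstinence v 14% | n per arm for 80% | Power at 400 per arm |
|---|---|---|---|
| 1.41 (2015 moderate referral) | 18.7% | 971 | 43.5% |
| 1.37 (text messaging in general) | 18.2% | 1,182 | 37.0% |
| 1.33 (as a true odds ratio) | 17.8% | 1,455 | 31.1% |
| 1.25 | 16.9% | 2,424 | 20.5% |
| 1.20 | 16.3% | 3,681 | 15.0% |

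The like-for-like loss from 1.41 to 1.37 is 43.5 − 37.0 = 6.5 percentage points. Any positive correlation within sessions would lower every power shown.

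**The case against.** **The stated odds ratio of 1.33 lies below the cited 1.37, so it is conservative even for Text.** As labelled, it does. A trial sized for a true 1.33 (1,455 per arm) would have about 87% power at 1.37. But the stated size does not use 1.33 as an odds ratio: 971 comes from 1.41, and the quoted power comes from 1.54. The label is cautious against 1.37; the figures built under it are not. What stands is that comparing the planning effect with 1.37 depends on sorting out that label.

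**The 1.37 is not this arm's effect.** Correct. It pools trials of varying intensity, and the Text arm also receives AWARD advice, a warning leaflet and a referral card that Control does not. It is a benchmark only and should not become the planning value without justification.

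**The intensity premise is limited.** Also fair. The Background ties the evidence to the clinical setting and extends it by assumption, to high- against low-intensity messaging. The article has no direct comparison of Text with the 2015 intervention. The premise therefore does not prove that the Text effect is smaller. It does leave the word conservative unsupported for that arm.

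**Underpowering is disclosed, and interval estimates are planned.** Both are true. The article says that 971 are required and only 400 per group are feasible, and it plans odds ratios with 95% confidence intervals. A reader might infer that low power was concealed; the text does not support that. The gap is narrower: the one power it discloses is not tied to a comparison.

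**Conclusion.** The point holds as a correction to stated figures. The 971 rests on a moderate-intensity effect, and the 57.3% on an odds ratio with no source or arm. Neither should be read as applying to Text v Control, and the effect is not shown to be conservative for that arm. Under the assumptions in the working, power for Text v Control at 400 per group is about 43% if Text does as well as the 2015 referral, about 37% at 1.37, about 31% at 1.33 and about 15% at 1.20.

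Three stronger readings are tempting but not supported:

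- That the Text comparison loses 20 points of power. This sets 37% at odds ratio 1.37 against a non-reproducing 57.3% at 1.54. At the effect actually used for sizing, the difference from 1.37 is about 6.5 points.
- That the trial could not detect the text-messaging effect it cites. At 37% power it is unlikely to, which is different.
- That 57.3% is sound for HAR and fails only for Text. It does not reproduce for either arm: 1.54 gives about 62% and the 2015 rates about 43%.

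**What to change.** In the sample-size section:

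1. Give a planning effect, with its source, and the power at 400 per group separately for HAR v Control and Text v Control, or state that Text v Control is not separately powered.
2. Drop the description of the effect as conservative for Text.
3. If no Text effect can be justified, show power as an assumption range, such as the table above, with 1.37 marked as a general benchmark and the absence of a clustering allowance stated.
4. Do not carry 57.3% over to HAR. Recalculate it from a stated control rate and a sourced effect.
5. Add that a non-significant Text v Control result will be reported with its odds ratio and 95% confidence interval and will not be taken as evidence that low-intensity referral is ineffective.

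The cost is a few sentences and a less favourable stated power for one comparison. Enrolment, procedures and the main analysis stay as they are.

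### The required size of 971 per arm contains no allowance for randomisation by recruitment session, and none is stated for the 57.3% power at 400 per arm

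*Protocol article*

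**What the plan says.** The unit of randomisation is the session. Under Randomization and blinding, "all participants will be randomly assigned to 1 of the 3 groups based on the recruitment session". The abstract has smokers "proactively recruited in the community from 68 clusters (recruitment sessions"), and the Recruitment section says: "A total of 68 recruitment activities will be organized in all 18 Hong Kong districts aiming to recruit 1200 participants over 3 months".

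The section Sample size and power analysis uses G*Power and the 3-month abstinence rates of the 2015 contest, where "the 3-month PPA for the moderate-intensity active referral intervention and the control group was 18.7 and 14%, respectively". At 80% power and "a significance level of 5%, 971 participants in each arm are required". It then says that "the maximum total sample size is 1200 (400 per group") and gives the power at that size as 57.3% for an effect size of 1.54. The section mentions no ICC, mean session size or design effect.

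**The concern.** Smokers recruited in one session share a place, a day and a team of ambassadors who deliver the on-site advice and, in the high-intensity arm, the booking. If their outcomes are at all alike, 400 smokers in about 23 sessions carry less information than 400 smokers randomised one by one. A sample size for such a trial has to be multiplied by a design effect, and power has to be computed on the reduced effective number.

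Two figures are at stake. The 971 is the benchmark against which the article measures its own shortfall. The 57.3% is what a reader would use to judge how much a null result means.

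**Working it through.** **Inputs.** From the article: 14% and 18.7%, 5% significance, 80% power, 971 per arm, 400 per arm, 57.3% power, 68 sessions, 1200 smokers. Two-sidedness is not stated; it is inferred because it reproduces the 971. The ICC is not given and is assumed.

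**1. Reproduce the 971.** Pooled two-proportion formula, independent participants:

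n = [1.960 × √(2 × p̄ × (1 − p̄)) + 0.8416 × √(p1(1 − p1) + p2(1 − p2))]² / (p2 − p1)²

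With p1 = 0.14, p2 = 0.187 and p̄ = 0.1635, the two terms are 1.0251 and 0.4393. Their sum squared is 2.1443; divided by 0.047² = 0.002209 this gives 970.7, so 971. Other variants do not match: 1,013 with continuity correction, 765 one-sided. An ICC of only 0.001 would already have given 987. The published figure therefore has a design effect of 1.00.

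**2. Design effect.** m = 1200/68 = 17.65 smokers per session, and 68/3 ≈ 22.7 sessions per arm. With equal sessions, DE = 1 + (m − 1) × ICC = 1 + 16.65 × ICC. Required size = 970.7 × DE, rounded up. Effective size of 400 = 400/DE.

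**3. Power.** The stated 57.3% corresponds to a standardised effect of 1.960 + 0.184 = 2.144. If it is an unclustered figure, clustering divides that by √DE, so power = Φ(2.144/√DE − 1.960). At ICC 0.01, 2.144/1.080 = 1.985, and Φ(0.025) = 0.51.

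**4. Detectable difference.** With control at 14%, solve the formula in step 1 for p2 so that n × DE = 400.

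| Assumed ICC | DE | Required per arm | Effective n of 400 | Power, from 57.3% | Detectable p2 at 80% power |
|---|---|---|---|---|---|
| 0 | 1.00 | 971 | 400 | 57.3% | 21.6% |
| 0.005 | 1.08 | 1,052 | 369 | 54% | 21.9% |
| 0.01 | 1.17 | 1,133 | 343 | 51% | 22.2% |
| 0.02 | 1.33 | 1,294 | 300 | 46% | 22.8% |
| 0.05 | 1.83 | 1,779 | 218 | 35% | 24.5% |

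**5. Is the 57.3% an unclustered figure?** The rates behind it are not stated. Taking an odds ratio of 1.54 on 14% gives 0.2156/1.0756 = 20.0%. At 400 per arm, two-sided and without clustering, power is then 62.4% by the pooled formula, 59.1% by Fisher's exact test and 58.8% with continuity correction. The last two lie within 2 points of 57.3%, so an unclustered calculation is the likely source, but the match is not exact as it is for the 971.

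**The case against.** **The stated power is not shown to be too high under every calculation.** A reader might infer that 57.3% is overstated whatever effect size or formula is used. The documents do not support that. With the pooled formula and an odds ratio of 1.54 on 14%, power is 62.4% at ICC 0, 58.9% at 0.005 and 55.8% at 0.01; it falls below 57.3% only above an ICC of about 0.0076. This stands. It does not show that clustering was allowed for, since unclustered calculations come close to 57.3%, but the power column above holds only if 57.3% is unclustered.

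**Not every shortfall comes from clustering.** A reader might set 57.3% beside the 43.5% that 400 per arm gives for 14% against 18.7% and blame the gap on sessions. That gap arises with no clustering at all. It comes from the change between the effect sizes 1.33 and 1.54 inside the section, which is a separate matter.

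**The ICC is unknown.** Sessions are booths in malls and public areas, and outcomes are collected individually by telephone. Nothing in the article supports a value as high as 0.05, and at 0.005 the loss is only about 3 points. This stands: the direction is certain for any positive ICC, the size is not.

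**The article already concedes low power, and 971 did not set recruitment.** Both are true; the 1200 is a ceiling set by resources and time. This lowers the severity. It does not make 971 the right benchmark for a cluster design.

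**GEE may handle it.** The Data analysis section plans GEE for the intervention effect but does not name the session as the cluster, and the main comparison is by chi-square test. If GEE does account for sessions, power is what a clustered calculation gives. If nothing does, a nominal 5% test has true size 2 × [1 − Φ(1.960/√DE)], about 7%, 9% and 15% at ICC 0.01, 0.02 and 0.05. Neither route restores the 971.

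**A condensed article may omit detail.** The exact match answers this: the published number itself contains no inflation.

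**Conclusion.** The point holds for the required size without reservation: 971 per arm is the answer for an individually randomised trial, and this trial randomises sessions. For power it holds in a conditional form. No ICC or design effect is stated for the 57.3%, and if that figure is unclustered, it falls by about 3 points at ICC 0.005, 6 at 0.01, 11 at 0.02 and 22 at 0.05. These sizes rest on assumed ICCs and equal sessions of 17.6; unequal sessions would lower power further.

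This is an omitted design effect and not an arithmetic slip, since the 971 reproduces exactly. It is a should-fix: it changes how a null result should be read, but not the randomisation, the outcomes or the number recruited.

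**What to change.** In Sample size and power analysis, state m = 17.6 and apply 1 + (m − 1) × ICC. Take the ICC from earlier contests if session-level data exist, which the article does not show; otherwise present a range of 0.005 to 0.05. Restate three figures on that basis: the required size per arm, the power at 400 per arm, with the two rates behind it, and the smallest detectable difference (about 22% to 25% against 14% over that range). Keep 1200 and describe the comparison as having limited power.

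The cost is a few lines of recalculation and less favourable stated figures; no extra recruitment is needed. The inconsistency between the effect sizes 1.33 and 1.54 should be corrected separately.
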